#### Research goal 2: Cost-consequence and cost-effectiveness analysis

A cost-consequence analysis is performed listing all relevant costs and effects without aggregating it into a ratio [47] allowing decision-makers to choose the outcome of particular interest to include in an economic analysis. Average costs and consequences of the whole cohort are compared with the subgroup of patients who have received a correct diagnosis according to the reference test. This enables the comparison of the current diagnostic practice costs and effects and the costs and effects of an ideal situation (a costless diagnostic test with 100% accuracy). The difference indicates the maximum possible achievable benefit of new biomarkers for AD and related disorders in terms of costs and health effects. Furthermore, a cost-effectiveness analysis is performed comparing current practice with diagnostic procedures that include emerging biomarkers. The change in costs is compared to the change in diagnostic accuracy to obtain a cost-effectiveness ratio in terms of costs per correctly diagnosed patient.

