### Subjects

For the study, 241 consecutive patients of the participating memory clinics who were suspected of having a primary neurodegenerative disease were included for participating in the study from October 2009 to May 2011; this included all patients with subjective and/or objective memory complaints. Eligibility criteria were chosen to represent the current clinical situation and enable generalisability to clinical practice (see Table 1). Informed consent was obtained from both the patient and the informal caregiver. Gender, age and reason for refusal were obtained for patients unwilling to participate.

**Table 1 T1:** Eligibility criteria for subject selection

*Inclusion criteria*	
-	All new consecutive patients of the participating memory clinics who are suspected of having a primary neurodegenerative disease
-	Mini-Mental State Examination: ≥ 20
-	Clinical Dementia Rating: 0 – 1
-	Availability of a reliable informer or proxy (who visits or contacts the patient at least once a week)
*Exclusion criteria*	
-	Normal Pressure Hydrocephalus, Huntington’s disease
-	Less than two years ago a transient ischaemic attack (TIA) or cerebral vascular accident (CVA) or TIA/CVA followed (within three months) by cognitive impairment
-	Psychiatric history (schizophrenia, bipolar disorder or psychotic problems (not otherwise specified), less than 12 months ago)
-	Major Depression according to the DSM-IV, less than 12 months ago
-	Cognitive problems due to excessive alcohol use (based on clinical judgement)
-	Brain tumour, epilepsy, encephalitis
-	Probably not available for follow-up

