### Baseline clinical diagnosis and reference diagnosis

Current clinical practice diagnosis is reflected by a consensus procedure among experts using baseline clinical information only, excluding any information of emerging biomarkers to prevent underestimating their accuracy.

The reference diagnosis is also determined by a consensus procedure among experts based on clinical information on the course of symptoms over a two-year time period and applying the core clinical criteria for the diagnosis of dementia due to AD [8] and core clinical criteria for the diagnosis of MCI due to AD [7]. Experts are kept blind for any information of the emerging markers under evaluation. Evaluating all cases by expert panel discussion meetings is highly time consuming. Therefore, first expert raters will assess all cases by means of an internet based form and if consensus is not reached the case will be discussed by a panel discussion meeting. The consensus diagnosis during the expert panel meetings is based on a modified Delphi method in which face-to-face discussions are held [45,46].

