### Sample size and missing data

A telephone interview is performed for patients who refuse follow-up assessments to determine the reason for refusal, possible cognitive decline and interference with daily activities, and to assess the CDR. Incomplete data will be imputed by means of a regression model. Complete missing data or data missing covariates will be imputed using Rubin’s multiple imputation (MI) procedure.

Sample size is based on an 80% accuracy of current clinical practice to determine correct aetiology [4] and 70% in non-demented patients [49]. Applying a type I error (α = 5%), type II error (β = 80%), drop-out rate of 10% and minimum clinically relevant difference of 10% accuracy increase requires 219 patients to be included in the study.

Contrary to clinical studies, economic evaluations are not based on testing hypotheses. Their goal is to assess decision uncertainty. Therefore, economic evaluations are restricted to the estimation of the uncertainty surrounding cost-effectiveness (expressed in a statistical confidence interval). Within this Bayesian framework, classical inference (and therewith a power analysis) is irrelevant [50].

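### The contrast read as the ceiling on biomarker benefit compares the whole cohort with a correctly diagnosed subgroup of different case mix, so it can have the wrong size or sign

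*Protocol article*

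**What the plan says.** The protocol article, under Research goal 2, fixes three things.

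- The contrast: "Average costs and consequences of the whole cohort are compared with the subgroup of patients who have received a correct diagnosis", where the reference test decides what counts as correct.
- Its meaning: the comparison is said to set current practice against "the costs and effects of an ideal situation (a costless diagnostic test with 100% accuracy").
- The conclusion: "The difference indicates the maximum possible achievable benefit of new biomarkers for AD and related disorders in terms of costs and health effects".

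Neither Research goal 2 nor Research goal 3 states any stratification, weighting or adjustment of this contrast. Research goal 3 then applies the mean costs and effects of correct and of incorrect diagnoses to every diagnostic procedure in the decision model.

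Two other places bear on whether the subgroup resembles the cohort. Under Sample size and missing data: "Sample size is based on an 80% accuracy of current clinical practice to determine correct aetiology [4] and 70% in non-demented patients [49"]. In the eligibility table: "Clinical Dementia Rating: 0 – 1", with all patients who have subjective or objective memory complaints admitted.

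**The concern.** For the subgroup mean to represent a perfect test applied to this cohort, correctly diagnosed patients must have the same mix of true disease and severity as everyone else. A perfect test changes the label of the misdiagnosed patients and keeps them in the population. The planned subgroup drops them.

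The protocol's own planning figures make the chance of a correct diagnosis depend on patient type, and the cohort is mixed. Costs and quality of life can be expected to depend on true disease and severity, whatever the label. The crude difference then contains two things: the effect of being correctly diagnosed, which is wanted, and the difference in case mix, which is not.

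At stake is a figure presented as a bound on the value of any new biomarker, in costs and in health effects. If the pooled averages in Research goal 3 are used as worded, a strategy with 100% accuracy is assigned exactly the correct-subgroup mean, and the model inherits the same distortion.

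**Working it through.** The documents give no figure for the ceiling itself, so there is none to reproduce. The stated sample size of 219 does not enter this check.

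**Inputs from the protocol article.** Accuracy in non-demented patients: a0 = 0.70. The 80% for aetiology can be read as accuracy in demented patients (a1 = 0.80) or as overall accuracy. With half the cohort demented, the second reading needs a1 = 0.90, since 0.5 × 0.90 + 0.5 × 0.70 = 0.80. Both are carried.

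**Assumptions, because the documents give none.** Demented share d, costs, and the saving s when a misdiagnosed patient is correctly diagnosed.

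**Step 1: case mix.** Overall accuracy is A = d·a1 + (1 − d)·a0. The demented share among the correct is dc = d·a1 / A. At d = 0.5:

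- a1 = 0.80: dc = 0.40 / 0.75 = 53.3%, a shift of 3.3 points.
- a1 = 0.90: dc = 0.45 / 0.80 = 56.3%, a shift of 6.25 points.

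For d from 20% to 70% the shift runs from 2.2 to 3.3 points (a1 = 0.80) or 4.3 to 6.25 points (a1 = 0.90, where overall accuracy runs from 74% to 84%). If accuracy is equal in both strata, the shift is 0.

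**Step 2: what the contrast estimates.** Let c1 and c0 be the costs of correctly diagnosed demented and non-demented patients, and let a misdiagnosis add s. Then:

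- true saving = cohort mean − mean with everyone correct = (1 − A)·s
- planned contrast = cohort mean − correct-subgroup mean = (1 − A)·s − (dc − d)·(c1 − c0)

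The last term is pure case mix. Set c0 = 100, d = 0.5 and s = 10. With a1 = 0.80 and c1 = 200, the cohort mean is 0.5 × (200 + 0.2 × 10) + 0.5 × (100 + 0.3 × 10) = 152.5, the correct subgroup is (80 + 35) / 0.75 = 153.33, and the all-correct mean is 150. Over a range of c1:

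| c1 | a1 = 0.80: planned / true | a1 = 0.90: planned / true |
|---|---|---|
| 150 | +0.83 / +2.50 | −1.125 / +2.00 |
| 200 | −0.83 / +2.50 | −4.25 / +2.00 |
| 300 | −4.17 / +2.50 | −10.50 / +2.00 |

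With s = 0 and c1 = 200 the truth is 0, but the contrast gives −3.33 or −6.25.

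**Step 3: when the sign flips.** The planned contrast has the wrong sign when s / (c1 − c0) is positive but below (dc − d) / (1 − A). At d = 0.5 this is 0.0333 / 0.25 = 13% (a1 = 0.80) or 0.0625 / 0.20 = 31% (a1 = 0.90). At d = 0.3 it is 11% or 23%.

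**Step 4: the same by reference class.** Assume AD prevalence 50% and two-year costs in kEUR of TP 30, FN 36, TN 12, FP 15. The all-correct mean is 0.5 × 30 + 0.5 × 12 = 21.0.

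- Sensitivity 0.9, specificity 0.7: cohort 13.5 + 1.8 + 4.2 + 2.25 = 21.75; correct subgroup (13.5 + 4.2) / 0.80 = 22.125. Planned contrast: EUR 375 added. True: EUR 750 saved.
- Sensitivity 0.7, specificity 0.9: cohort 10.5 + 5.4 + 5.4 + 0.75 = 22.05; correct subgroup (10.5 + 5.4) / 0.80 = 19.875. Planned contrast: EUR 2,175 saved. True: EUR 1,050 saved.

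Overall accuracy is 80% in both cases, yet the error goes in opposite directions.

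**The case against.** The other side has several fair points.

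- *Role.* A reader might take this contrast as the main result of goal 2, or as a criterion on which biomarkers stand or fall. The documents do not support that. Goal 2 also has a separate analysis of cost per correctly diagnosed patient, goal 3 draws on literature and expert opinion, and nothing makes the ceiling a decision rule. This stands and lowers the severity.
- *Which diagnosis counts.* A reader might infer that correctness is judged on the expert panel's baseline diagnosis and not on the one the clinic gave the patient. The article says "Current clinical practice diagnosis is reflected by a consensus procedure among experts using baseline clinical information only", but that describes the accuracy comparison. Research goal 2 makes the reference test the standard of correctness and does not say whose diagnosis was received. This is an ambiguity to clear up and not an established error.
- *Inputs.* The 80% and 70% are planning values, and prevalence, costs and savings above are all assumed. Eligibility at MMSE 20 or more and CDR 0 to 1 narrows the severity range. A reader might infer that the estimate will have the wrong sign, or that advanced cases are over-represented; the documents establish neither. They do imply unequal accuracy by dementia status, and that is enough for the case mix to differ.
- *Condensed article.* Details may sit in a fuller plan. That does not answer the point, because the contrast and its interpretation are both printed.
- *Sensitivity analysis.* The one planned for the model covers variation between patients and uncertainty in parameters. Neither removes a case-mix difference.
- *Feasibility of a remedy.* At 80% accuracy about 241 × 0.20 = 48 patients are misdiagnosed. In the first scenario of Step 4, false negatives number about 241 × 0.05 = 12. A heavily adjusted comparison of correct with incorrect diagnoses is barely estimable. This stands and shapes the fix.

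**Conclusion.** The point holds as a should-fix. The planned difference is not the effect of a perfect test on this cohort, because the correctly diagnosed subgroup has a different case mix under the protocol's own accuracies. The bias vanishes only if accuracy is equal across patient types, if types have equal costs and effects, or by chance cancellation. The protocol assumes none of these.

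The shift in demented share is a few percentage points. Multiplied by an assumed cost gap of EUR 20,000, it moves the difference by EUR 667 (3.33 points) or EUR 1,250 (6.25 points) per patient with no benefit at all. Whether that is small or decisive depends on the real cost gap and the real effect of correct diagnosis, which the documents do not give. Wrong size and wrong sign are shown to be possible; the actual direction and size are unknown. The goal 3 model is affected only if its averages are pooled over reference classes, as the wording suggests.

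**What to change.** 1. Compute the all-correct mean by taking the mean of correctly diagnosed patients within each reference class and weighting to the whole cohort's class distribution. In Step 4 this gives 21.0 in both scenarios. Because the stated accuracies differ by dementia status, also stratify by baseline severity, such as CDR, where numbers allow. Report the observed cohort mean minus this figure, with its interval, for costs and for health effects.
2. In Research goal 3, apply separate averages for true positives, false negatives, true negatives and false positives in place of pooled averages for correct and incorrect diagnoses.
3. Keep the crude contrast as descriptive only, withdraw its reading as an upper limit on benefit, and state that confounding within class remains after weighting.
4. State whether the diagnosis received is the clinic's or the panel's.

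The cost is a change of wording and a simple weighting. Reference class, CDR and MMSE are already planned, so no new visits are needed. If the clinic's own diagnosis is chosen in item 4, it may have to be taken from the record, since the article does not show that it is a study variable. The downside is somewhat wider intervals, sparse misdiagnosed cells in the model, and a less simple statement of the result.

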## Study aim

The general aim of the study is to assess the clinical and economic value of current, emerging and novel (to be developed) techniques for an early diagnosis of AD and related disorders. In this paper the methodology is described.

The research goals are:

1. To assess the diagnostic test accuracy of the current clinical standard diagnostic work-up and emerging diagnostic biomarkers in MRI, PET and CSF

2. To assess costs and effects for the follow-up period to perform a cost-consequence and cost-effectiveness analysis

3. To develop a preliminary economic model to assess the uncertainty surrounding long-term cost-effectiveness of diagnostic strategies

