### Data assessment

Each centre collects a minimum dataset of clinical information based upon the dataset protocol used for The String of Pearls Initiative – Pearl Neurodegenerative Diseases (http://www.string-of-pearls.org), cost data and data on emerging biomarkers. Table 2 provides an overview of all patient and informal caregiver assessments. Assessments take place at baseline and at 12 and 24 months follow up during a visit (from both patient and informal caregiver) to the memory clinic. Furthermore, several questionnaires were composed in a booklet to measure resource consumption and quality of life. This is filled out by the informal caregiver at baseline, 3, 12 and 24 months.

**Table 2 T2:** Overview of patient and informal caregiver assessments at baseline and follow-up

**Outcome measure**	**Operationalization/type of instrument**	**B**	**T3**	**T12**	**T24**

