## Discussion

This research protocol describes the methods used to assess the clinical and economic value of new diagnostic approaches for the diagnosis of AD. A delayed-type cross-sectional accuracy study design is chosen because a randomized clinical trial comes with ethical issues, long follow-up time and limited power. Two hundred forty one consecutive patients suspected of having a primary neurodegenerative disease are followed up for two years and a reference diagnosis is determined by an independent consensus expert panel. Eligibility criteria are chosen to maximally reflect a patient cohort within clinical practice.

Several other multi-centre trials study the relative value of new biomarkers for early evaluation of AD and related disorders. The Alzheimer’s Disease Neuroimaging Initiative (ADNI) in North America is aimed to identify neuroimaging measures and biomarkers associated with cognitive and functional changes in healthy elderly subjects and in subjects who have MCI and AD [51]. Furthermore, the ‘Development of Screening Guidelines and Clinical Criteria for Predementia AD’ (DESCRIPA) study is aimed to develop screening guidelines for predementia AD in the general population [52]. Both include markers in PET, MR imaging and CSF. The uniqueness of this study is the assessment of resource utilization and quality of life to enable an economic evaluation. Furthermore, the decision analytic model enables the evaluation of the optimal diagnostic strategy and the evaluation of diagnostic techniques to be developed during the study in sub-cohorts of the study population. At last, without a disease modifying treatment, the added value of biomarkers is uncertain. Therefore, the availability of such treatment is explored in the sensitivity analysis.

The study has some limitations. It focuses on applying new tests for diagnostic or prognostic goals. Screening and treatment monitoring are outside the scope of this study. A follow-up period of two years was taken as a compromise to maximise the time for the disease to express symptoms of progression (to prevent false negative reference diagnoses) and to minimize the time to prevent the start of a new disease episode after the baseline assessment (to prevent false positive reference diagnosis). It may take up to 10 years before all symptoms of dementia come to expression in subjects with AD pathology [53].

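### The goal 2 difference is called the maximum benefit of biomarkers, but it is at most a two-year ceiling under current care, and only if the groups are comparable

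*Protocol article*

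**What the plan says.** All references are to the protocol article.

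- **Research goal 2, the contrast.** "Average costs and consequences of the whole cohort are compared with the subgroup of patients who have received a correct diagnosis according to the reference" […]. The subgroup stands in for a free test that is never wrong.
- **Research goal 2, the interpretation.** "The difference indicates the maximum possible achievable benefit of new biomarkers for AD and related disorders in terms of costs and health effects". No horizon or treatment setting is attached.
- **Study aim, goal 2.** "To assess costs and effects for the follow-up period to perform a cost-consequence and cost-effectiveness analysis".
- **Data assessment.** The booklet that carries resource use and quality of life stops at two years: "This is filled out by the informal caregiver at baseline, 3, 12 and 24 months".
- **Research goal 3.** Long-term cost per QALY is estimated in a separate decision model. Its sensitivity analysis is also where earlier diagnosis, other test sequences and possible new disease-modifying drugs are examined.
- **Discussion.** "without a disease modifying treatment, the added value of biomarkers is uncertain", and for that reason treatment availability is explored in the sensitivity analysis. In the paragraph on limitations: "It may take up to 10 years before all symptoms of dementia come to expression in subjects with AD pathology".

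**The concern.** A maximum is a strong claim: it tells a decision-maker that nothing beyond this figure can be gained. The figure comes from two years of observation under existing care, while the same protocol names further routes to benefit and gives them to another analysis. A small or null two-year difference, reported in the protocol's words, could be read as showing that biomarkers cannot bring more than this. The goal 3 model might point the other way, with goal 2 carrying the stronger word.

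The contrast is also between a cohort and a non-randomised subgroup of it. Even as a two-year ceiling, it holds only if patients who are easy to diagnose do not differ in prognosis and cost from those who are hard to diagnose.

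**Working it through.** The disputed sentence gives no figure to reproduce. The check is first logical, then illustrative.

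**1. What the difference contains.** Let p be the proportion correctly diagnosed, and M_c and M_i the mean two-year QALYs of correctly and incorrectly diagnosed patients. The cohort mean is p·M_c + (1−p)·M_i. Hence

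M_c − cohort mean = (1−p)·(M_c − M_i) = (1−p)·D.

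The planning values in Sample size and missing data are p = 0.80 overall and 0.70 in non-demented patients, so the declared maximum is 20% or 30% of D. D is measured over follow-up under the care then available. It holds nothing that accrues after month 24 and nothing from a drug not yet in use. If D = 0, the declared maximum is zero whatever happens later. Any later or treatment-related gain that adds to the two-year gain exceeds it.

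**2. Horizon (assumed patterns).** Let d(t) be the yearly difference, m yearly mortality and r the discount rate. The ratio of 10-year to 2-year benefit is

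R = ∫₀¹⁰ d(t)·e^(−mt)·(1+r)^(−t) dt ÷ ∫₀² d(t)·e^(−mt)·(1+r)^(−t) dt.

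For constant d, with k = m + ln(1+r), this is R = (1 − e^(−10k)) / (1 − e^(−2k)).

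| Assumed pattern | Calculation | R |
|---|---|---|
| No difference after month 24 | numerator = denominator | 1.0 |
| Halves each year, m = r = 0 | (1 − 2⁻¹⁰)/(1 − 2⁻²) = 0.999/0.75 | 1.33 |
| Constant, m = 10%, r = 4% | k = 0.139; 0.7515/0.2430 | 3.09 |
| Constant, m = 5%, r = 1.5% | k = 0.065; 0.4774/0.1217 | 3.92 |
| Constant, m = r = 0 | 10/2 | 5.0 |

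Ten years is used only as an example of a longer horizon.

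**3. Treatment (assumed gains).** Suppose each newly correct patient gains an extra e QALY within two years from a new drug. The benefit per cohort patient is (1−p)·(D + e). At p = 0.80 and D = 0.05 the declared maximum is 0.2 × 0.05 = 0.010. With e = 0.05, 0.10 or 0.20 the benefit is 0.020, 0.030 or 0.050. With D = 0 the declared maximum is 0, while the benefit is 0.010 to 0.040.

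**4. Comparability (assumed values).** Suppose the diagnosis has no effect at all, two-year QALYs are 1.2 in demented and 1.6 in non-demented patients, and accuracy in non-demented patients is 0.70.

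- Demented share 30%, accuracy 0.8 in demented patients: the cohort mean is 0.3 × 1.2 + 0.7 × 1.6 = 1.480. The correct-subgroup mean is (0.24 × 1.2 + 0.49 × 1.6)/0.73 = 1.4685. The difference is −0.0115.
- Demented share 50%, accuracy 0.9 in demented patients: the cohort mean is 1.400. The correct-subgroup mean is (0.45 × 1.2 + 0.35 × 1.6)/0.80 = 1.375. The difference is −0.025.

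Case mix alone can therefore give a negative maximum benefit.

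**The case against.** The best defence is that context supplies the limits. The sentence stands under goal 2, which the Study aim ties to the follow-up period. The sentence before it sets current diagnostic practice against a perfect, free test. On that reading the maximum is taken over test accuracy and test cost only, and goal 3 covers the rest whatever goal 2 shows. This is a sensible reading and the one the sponsor should write down. It does not rescue the sentence as it stands, which speaks of the benefit of new biomarkers in general and states neither limit.

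Other parts of the defence stand and narrow the point:

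- A reader might infer that the protocol contradicts itself by giving a 10-year span of benefit, so that the true ceiling is five times larger. The 10-year remark concerns how long symptoms take to be fully expressed, and it is made as a limitation of the two-year reference diagnosis. It does not say how long a correct diagnosis pays off. Five is the result of assuming a constant difference. Patients are reassessed at 12 and 24 months, so misdiagnoses may be corrected and the difference may shrink.
- A reader might infer that the protocol makes the value of biomarkers depend on a new drug. It says only that the added value is uncertain without one. That no such drug was in use in the cohort is implied by the Discussion, not stated.
- A reader might fear a stopping decision based on this figure. No section uses it that way. The cost-consequence analysis lists outcomes for decision-makers to choose from, and the verb is the mild one of indicating.

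**Conclusion.** The sentence is wrong as written, in a limited way. The goal 2 difference is at most a ceiling on what perfect accuracy and a free test could add within two years under current management, and it is that only if correctly and incorrectly diagnosed patients are comparable. It is not a general upper bound, because the protocol itself places long-term cost-utility, earlier diagnosis and possible disease-modifying treatment outside it.

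The shortfall cannot be derived from the documents. The ratios of 1 to 5 come from assumed patterns and are not limits: a difference that widened over time would give more. The conclusion needs none of these values, only that some additional benefit can arise later or through treatment. Data collection and the diagnostic accuracy analysis are unaffected; what changes is what the study may claim from goal 2.

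**What to change.** 1. In Research goal 2, replace the claim of a maximum with *two-year difference under current management, assuming comparable groups*.
2. Report the ceiling from the goal 3 model instead: sensitivity = specificity = 1, test cost 0, the model's long-term horizon, with and without the treatment scenario already planned for the sensitivity analysis.

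The cost is one changed sentence and one or two extra runs of a model that will be built anyway; no new data are needed. The downside is that the ceiling then rests on model assumptions, which should be stated and varied. Relabelling does not remove possible confounding by case mix, so the comparability assumption must stay visible wherever the two-year difference is reported.

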#### Research goal 3: Decision analytic model

Finally a decision analytic model is built which provides a framework combining available evidence from different resources among which (accuracy) results from the study, literature and expert opinion. A decision analytic model can be defined as a set of mathematical relationships that form a structure reflecting the natural progression of a disease. By simulating patients or fractions of a population, these models enable the estimation of the likelihood of each consequence and its corresponding costs and effects [48]. It is applied to evaluate the short-term cost-effectiveness in terms of cost per correct diagnosis and long-term cost-utility in terms of cost per quality adjusted life year gained of diagnostic strategies under evaluation. Utility scores will be used to calculate Quality Adjusted Life Years (QALY). Patients who pass away during the year covered by the evaluation will be given a utility score of zero from the exact time of death. QALYs will be derived using the trapezium rule. A societal viewpoint will be adopted including the evaluation of all relevant costs and effects to calculate the societal benefits.

The cohort design facilitates the evaluation of many different diagnostic procedures by varying the place of a new diagnostic marker in the clinical pathway. Each procedure generates specific proportions of correct or incorrect diagnoses. Average costs and effects of correct and incorrect diagnoses are applied to calculate the total costs and effects of each procedure.

Sensitivity analysis will be performed taking into account both first order uncertainty regarding variation between patients in a homogeneous group and second order uncertainty regarding the true value of the parameters included in the model. This also enables the evaluation of an earlier diagnosis, different test sequences and the effect of possible new disease modifying drug treatments.

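### The goal 2 cost-effectiveness ratio names current practice as comparator, which is not the right increment when several biomarker procedures compete

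*Protocol article*

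**What the plan says.** The protocol article, section on research goal 2, sets the comparison: "a cost-effectiveness analysis is performed comparing current practice with diagnostic procedures that include emerging biomarkers". The sentence after it defines the measure: "The change in costs is compared to the change in diagnostic accuracy to obtain a cost-effectiveness ratio in terms of costs per correctly diagnosed patient".

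More than one biomarker procedure is in view. Table 3 lists CSF, PET and MRI markers. The Analyses section evaluates the core clinical criteria, the research criteria and several exploratory decision rules. The section on research goal 3 says: "The cohort design facilitates the evaluation of many different diagnostic procedures by varying the place of a new diagnostic marker in the clinical pathway". It adds test sequences under the sensitivity analysis: "This also enables the evaluation of an earlier diagnosis, different test sequences and the effect of possible new disease modifying drug treatments".

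The goal 3 model produces totals for every option: "Average costs and effects of correct and incorrect diagnoses are applied to calculate the total costs and effects of each procedure". Its scope is given as "It is applied to evaluate the short-term cost-effectiveness in terms of cost per correct diagnosis and long-term cost-utility". The Discussion states that "the decision analytic model enables the evaluation of the optimal diagnostic strategy".

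None of these sections mentions an increment between two biomarker procedures, a dominance step, a net-benefit comparison or a willingness-to-pay threshold.

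**The concern.** A patient is worked up by one procedure or another, so the procedures are best read as mutually exclusive options. With two options, the ratio against current practice is the incremental ratio. With three or more, the decision to move to a dearer procedure turns on what it adds to the next cheaper procedure worth considering. A ratio against current practice credits the dearer procedure with accuracy that the cheaper one already delivers.

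Two things can go wrong for a reader of the goal 2 results. A procedure that is both dearer and less accurate than another still receives a finite ratio, which may look acceptable. And a procedure that is slightly more accurate but much dearer can appear good value although its additional correct diagnoses are expensive.

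**Working it through.** The plan gives no procedure costs, accuracy gains or cost-effectiveness ratios, so there is no figure of its own to reproduce. The mechanism can be checked on assumed inputs.

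**Inputs**
- Current practice: accuracy 80%, from the section on sample size and missing data; cost set to 0 as reference.
- Procedure A: extra cost 300, accuracy 88% (assumed).
- Procedure B: extra cost 1,000, accuracy varied (assumed).
- Threshold of 20,000 per extra correct diagnosis (assumed).

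**Formulas**
- Ratio against current practice = extra cost / (accuracy − 0.80).
- Ratio of B against A = (1,000 − 300) / (accuracy of B − 0.88). If B is no more accurate than A, A dominates B.
- Net benefit = 20,000 × (accuracy − 0.80) − extra cost.

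**Results**

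A against current practice: 300 / 0.08 = 3,750. Net benefit: 20,000 × 0.08 − 300 = 1,300.

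| Accuracy of B | B against current practice | B against A |
|---|---|---|
| 84% | 1,000 / 0.04 = 25,000 | dominated |
| 87% | 1,000 / 0.07 = 14,286 | dominated |
| 88% | 1,000 / 0.08 = 12,500 | dominated |
| 89% | 1,000 / 0.09 = 11,111 | 700 / 0.01 = 70,000 |
| 90% | 1,000 / 0.10 = 10,000 | 700 / 0.02 = 35,000 |
| 92% | 1,000 / 0.12 = 8,333 | 700 / 0.04 = 17,500 |

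- At 87%, B passes the threshold against current practice although A is cheaper and more accurate.
- At 89% and 90%, B passes against current practice but fails against A. At 89% its net benefit is 20,000 × 0.09 − 1,000 = 800, below A's 1,300.
- At 92%, A has the lower ratio against current practice, yet B is the better choice: 17,500 is below the threshold, and B's net benefit is 20,000 × 0.12 − 1,000 = 1,400. Picking the lowest ratio against current practice would therefore fail too.
- At 84%, B already fails against current practice, so the common comparator does no harm.

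**A second set of assumed inputs.** A costs 500 and gains 6 points; B costs 2,000 and gains 8. Against current practice: 500 / 0.06 = 8,333 and 2,000 / 0.08 = 25,000. B against A: 1,500 / 0.02 = 75,000, three times its ratio against current practice.

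**A case where the dearer ratio stays as it was.** A costs 500 and gains 2 points (500 / 0.02 = 25,000); B costs 2,000 and gains 10 (2,000 / 0.10 = 20,000). B against A is 1,500 / 0.08 = 18,750, lower than A's own ratio. A is therefore extendedly dominated and drops out, and B's correct ratio remains 20,000 against current practice.

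**The case against.** The strongest reply has four parts.

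1. **Goal 2 names one comparison but does not exclude others.** A reader might infer that current practice is the only comparator. The text does not say so, and that reading should not be pressed. It remains true that it is the only comparator named.

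2. **The optimal strategy comes from goal 3.** A reader might infer that the goal 2 ratio makes the optimal strategy wrong. The documents do not support that. The Discussion attributes the optimal strategy to the decision model, which calculates total costs and effects for each procedure and states no restriction to current practice. Those totals yield every pairwise increment. This part of the reply stands. It does not settle goal 2, which is a separate research goal with its own ratio, and the model section gives no rule for comparing procedures either.

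3. **A common baseline does not distort net benefit, and listing the ratios side by side can reveal poor value.** The first half is right: subtracting the same reference from every option leaves the net-benefit order unchanged. But the plan specifies a ratio. In the 89% case the two ratios, 3,750 and 11,111, both pass the assumed threshold, and neither shows the 70,000 increment. A reader could recover it only if costs and gains are reported beside the ratios.

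4. **An article may leave such detail to the full protocol.** This would answer a silence. Here the article does fix a comparator and a ratio, and these do not suffice for the many-procedure comparison it describes. The reply does have force where a single biomarker procedure, such as the research criteria, is set against current practice; there the stated ratio is correct.

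**Conclusion.** The point holds in a limited form. The goal 2 ratio is valid for a two-option comparison. With several competing procedures it can make a dominated procedure look acceptable, or understate the cost of a dearer procedure's extra accuracy over a cheaper one.

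The size is illustrative only. On the assumed inputs the understatement ranges from about twofold (8,333 against 17,500) to about sixfold (11,111 against 70,000), and in other configurations there is none. The conclusion rests on reading the procedures as mutually exclusive options for one patient and on the goal 2 ratios being read by themselves; the documents state no adoption threshold or selection rule. They do not show that the goal 3 result would be wrong, only that no stated comparison rule protects it.

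**What to change.** In the section on research goal 2, keep the measure (cost per correct diagnosis) and replace the comparison rule:

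- order all procedures, current practice included, by mean cost;
- remove dominated and extendedly dominated procedures;
- report each remaining ratio against the next cheaper non-dominated procedure, or compare net benefit across all procedures at once.

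State the same rule for the goal 3 model outputs, for both cost per correct diagnosis and cost per QALY. Reporting each procedure's mean cost and accuracy beside its ratio would let readers check the increments.

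The change uses the same costs and accuracies, so it needs no new data, only revised wording and slightly more analysis work. Some ratios for dearer procedures will become less favourable, though not necessarily all.
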